### Surgical technique

2.4

Percutaneous kyphoplasty was performed in the prone position under local anesthesia, and all procedures were conducted using a unilateral or bilateral transpedicular approach. A needle and an inflatable balloon were inserted through the working channel into the fractured vertebral body under visualization with lateral and anteroposterior fluoroscopy. A kyphoplasty balloon was then used to inflate and create a cavity. Subsequently, the balloon was deflated and removed, followed by filling with viscous polymethylmethacrylate. The cannula was removed after the bone cement was fixed. Patients were allowed to move around gradually under the protection of thoracolumbosacral orthosis 2–3 days postoperatively.

### Date collection

2.5

First, preoperative demographic and clinical baseline data of eligible participants, including age, sex, body mass index (BMI), bone mineral density (BMD), time from injury to surgery, fracture location, and previous OVCF, will be collected according to the medical records.

Besides, this study will collect matched preoperative spine CT images and MRIs of each patient for DL model training and validation. For both CT and MRI scan, all subjects are scanned in supine position. Image acquisition details of the internal dataset are described as follows: CT data acquisition of the spine are performed on a 64-slice MDCT scanner (Discovery CT750 HD, GE Healthcare, United States). A slice thickness of 1.25 mm and an in-plane resolution of 512 × 512 pixels were set for CT scans. Spine MRI is performed using a 3.0-T magnetic resonance system (Magnetom Verio, Siemens, GER). The scan parameters are as follows: T1WI (TR/TE, 400–600/8 ms), T2WI (TR/TE, 3,000–3,100/100 ms), T2WI-FS sequence (TR/TE, 4,000–4,200/70–80 ms), axial in-plane resolution: 256 × 224 pixels, axial slice thickness 3 mm, and intersection gap of 0.5 mm. Sagittal images were then reconstructed with an in-plane resolution of 320 × 256 pixels and a slice thickness of 4 mm. Noteworthily, most patients with OVCF usually complain of back pain at first visit, which sometimes is difficult to differentially diagnosed with degenerative spinal disease, especially in whom without definite trauma history. Hence, the reserved initial MRI may not contain continuous axial images at the fracture vertebral level in specific individuals. Therefore, we choose to collect continuous sagittal T2WI of MRI combined with continuous axial CT images, to obtain maximum information from multimodal image sources. For external dataset, spine CT is performed on a 16-slice CT scanner (SOMATOM Emotion 16, Siemens Healthcare, Germany). A slice thickness of 3.75 mm and an in-plane resolution of 512 × 512 pixels were set. MRI is performed using the same 3.0-T magnetic resonance system (Magnetom Verio, Siemens, GER) as in the internal dataset. The scan parameters were generally same except for an axial in-plane resolution of 384 × 269 pixels, an intersection gap of 0.3 mm, and a sagittal in-plane resolution of 384 × 326 pixels. All image data will be stored in DICOM files for further processing. The retrospective internal dataset will be divided into training and validation sets at a 9:1 ratio.

### Diagnostic criteria for BCL and dataset labeling

2.6

Although postoperative CT is the most accurate approach to detect BCL, it is not necessary for all types of BCL (22), and the postoperative X-ray can achieve satisfactory sensitivity (23). Therefore, either the immediate postoperative spine CT or X-ray will be checked to confirm the occurrence of BCL. BCL was defined as the presence of extravertebral cement. Further, we proposed modified four subtypes of BCL are differentiated by the location of the extravertebral cement according to Bermejo et al. (9): (1) Type I, leaking through the segmental vein; (2) Type II, leaking through the cortical defect to perivertebral soft tissue; (3) Type III, leaking into intervertebral disk; (4) Type IV, leaking into the spinal canal (through basivertebral vein or cortical defect) (Figure 2).

### Preparation and development of DL model

2.7

All algorithms will be conducted in Python 3.8.0 running on the Ubuntu 18.04 operating system, based on the hardware including Intel (R) Xeon (R) CPU E5-2620 V4, Titan V 12G GPU.

The schema of the expected neural network pipeline is shown in Figure 1A. The DL system consists of two main steps: (1) Preprocessing, including resampling, scale adjustment, vertebral segmentation, and bounding box generation; (2) Classification. Our team has once designed an interactive U-net neural network architecture to perform the CT vertebral segmentation task, and the vertebral segmentation Dice coefficient reached 96.8% ± 1.2% (24). The approach begins with an interactive initialization locator module, which allows surgeon manually determined the target vertebrae, followed by automatically segmentation. The interactive design omits the iterative search of freshly fractured vertebrae and avoids the possibility of localization error, especially in patients with multi-level or previous fractures. Further training on MRI data and corresponding U-net neural network architecture optimization will be conducted. Second, a bounding box generation technique (25) was performed to reduce the search area for CNN classifier, and to reserve sufficient information beyond the vertebrae of the initial image such as paravertebral vessels. The bounding box starts with contour detection of segmentation mask (in both axial and sagittal images) and cropped out of the original image (25).

Next, intermediate multimodal fusion CNN-based classifiers will be designed to integrate the information of axial CT image and sagittal MRI (26). The framework of the applied architecture is shown in Figure 3. The approach begins with transforming input data (preprocessed CT and MR images) into higher-level representations by elaborate feature extraction and selection. A shared representation layer is then fused by the representations from different sources. Finally, several CNN-based classifiers, such as VGG, ResNet, Yolo, etc., were used to perform final multi-task predictions.

**Figure 3 fig3:**
[figure not shown]
Architecture of the deep learning prediction model.

### Outcomes

2.8

The primary outcome measures will be the main exactitude performance of DL model for binary predicting (0/1) different subtypes of BCL, including sensitivity, specificity, and the area under the receiver operating characteristic curve (AUROC), in both internal and external test sets. Secondary outcomes include other exactitude performance such as accuracy, precision, and F1 score. Additionally, the reliability of the model will be evaluated by calculating its consistency with reference standards and comparing it with that of clinician prediction.

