## Introduction

1

The incidence of osteoporosis is escalating as the global population ages, causing a concomitant increase in osteoporotic vertebral compression fracture (OVCF). Annually, approximately 1.4 million new onset OVCFs are reported globally (1–3). OVCF causes low back pain, vertebral deformity, and severe functional impairment, which profoundly diminish the quality of life in the elderly population and impose substantial burdens on families and healthcare systems (4–6). Fortunately, percutaneous kyphoplasty (PKP) has become a widely adopted and effective clinical intervention for OVCF. PKP, as a minimally invasive approach, exhibits several merits, including substantial pain alleviation, partial vertebral height restoration, and early mobilization facilitation (7, 8).

However, bone cement leakage (BCL) has drawn significant attention as one of the most prevalent PKP complications, with incidence rates ranging of 5–80% (9, 10). Although a large proportion of BCLs are asymptomatic, poor outcomes still occur in specific individuals. Meanwhile, the type of complications significantly varies among different leakage locations. In particular, cement leakage into the spinal canal causes spinal cord and/or nerve root compression, potentially causing radicular pain and neurological dysfunction, which may require additional nerve decompression surgery (11). Furthermore, cement leakage into the paravertebral vein may cause serious conditions such as pulmonary embolism, cardiac perforation, cerebral embolism, and even fatality (12, 13). Additionally, cement leakage into the intervertebral disk exacerbates disk degeneration and increases the risk of adjacent vertebrae fractures (11, 14). Consequently, minimizing the incidence of BCL has become a crucial concern for surgeons. However, effective and intelligent methods to precisely predict BCL preoperatively remain lacking.

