### Sample size

2.9

The data for DL in this study will be a matched series of spinal axial CT and sagittal MRI so that each participant represents one sample. According to a sample size determination study based on DL models and 3D images, the receiver operating characteristic (ROC) curve of classification accuracy became stable when the training sample size increased to 200, and reached a high 98% classification accuracy at a training sample size of 1,000 per class (27). In the present study, binary predictions are warranted for each subgroup of BCL, so at least 250 participants in the internal dataset, containing 200 (80%) for the training set, as the minimal sample size will be acceptable for accurately performing the task. However, more eligible patients up to 1,250 participants, containing 1,000 (80%) for the training set, will be enrolled to achieve a higher accuracy.

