### Statistical analysis

2.10

All data will be analyzed using *Python* 3.8.0. The confusion matrix of DL model and readers in detecting Type I–IV of BCL will be used to evaluate the predicting performance. Quantitative evaluation metrics containing accuracy, sensitivity, specificity, precision, and F1 score, will be calculated based on the confusion matrices. Meanwhile, the ROC curve for binary classification will be plotted and AUROC will be calculated. Linearly weighted Cohen’s kappa coefficient between Reader 3, Reader 4, and the DL model with the reference standard will be used to assess the interobserver and model’s reliability. Statistical significance is set at *p* < 0.05.

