A primary concern of spine surgeons during PKP is reducing the occurrence of BCL. Despite rigorous efforts, the rate of BCL remains alarmingly high, even up to 80% (9, 10). This is particularly disturbing as certain types of leakage can cause severe complications, even mortality. Notably, leakage remains an unavoidable risk even if the operator is an experienced specialist. Currently, intraoperative C-arm fluoroscopy is still the most predominant approach for monitoring BCL, yet its image quality is even inferior to that of plain radiographic images (23). This hampers the early and accurate detection of BCL, particularly leakage into the spinal canal, during the intervention. Consequently, developing an effective and reliable preoperative BCL prediction model to facilitate precise individualized risk prediction in patients with OVCF is crucial. To date, only a few studies attempted to predict BCL using several traditional ML models (16–18). Li et al. used six ML models to predict BCL by incorporating clinical baseline characteristics and surgery-related variables, and the AUROC for these models was 0.633–0.898 (16). Further, Hu et al. incorporated radiographic variables from 425 patients to predict BCL using five ML models and revealed that the XGBoost demonstrated the highest AUROC of 0.8819 (17). However, these traditional ML models had inherent limitations, such as depending on manually extracted features and a lack of subtyping for BCL, which restricted their generalization. Recently, an initial attempt has been made to predict BCL using a DL model, but it still relied on manual image feature extraction (17). In addition, the predictive performance of this DL model was inferior than that of the XGBoost model. This indicates that while DL has notable advantages in several domains like image, language, and audio processing, tree-based ML methods have achieved robust predictions more easily than DL for small-scale data (17). However, with the rapid advancements in artificial intelligence technology, it is currently attractive and of great potentiality in developing more accurate and concise DL models by large datasets for predicting BCL.

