Overall, our study presents several significant advantages over previous predictive models. First, our model directly uses preoperative CT and MRI images as inputs. Previous studies have emphasized the clinical significance of radiology-related variables such as cortical destruction, intervertebral cleft, bone mineral density, fracture severity, fracture type, and basivertebral foramen sign in BCL prediction (9, 17, 29–31). In particular, Hu et al. determined only preoperative imaging parameters and intraoperative cement volume as independent risk factors for BCL after analyzing over 20 potential risk factors, including baseline characteristics, medical history-, surgery-, and radiology-related variables (17). Hence, a purely image-based DL prediction model is both adequate and reasonable. The DL model adaptively learns feature information from preoperative images without manual intervention, which enables seamless integration into current clinical workflows (32). Second, BCL is an immediate intraoperative complication without being affected by various confounding factors during long-term follow-up, improving the credibility and interpretability of our predictive model. Third, our model not only predicts the occurrence of BCL during PKP, but also enables further subtypes of leakage. Such predictive results are instrumental for clinicians in developing more thorough and personalized treatment plans. Next, our models will be trained on relatively large sample size datasets and validated with prospective, multi-center datasets, which not only improves the performance of the model, but also improves its generalization and applicability across different healthcare settings. Moreover, we will compare the prediction capability of our model with that of clinicians to test its reliability to further evaluate the performance of the model, which will provide a more comprehensive and objective evaluation of the model’s performance.

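### The per-subtype primary measures do not separate subtype discrimination from any-leak detection, so alone they cannot support the claim that the model predicts leak subtype as well as occurrence

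*Protocol article*

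**What the plan says.** The protocol article describes one yes/no task per subtype in three places.

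- Section 2.8 (Outcomes) sets the primary measures as performance in "binary predicting (0/1) different subtypes of BCL, including sensitivity, specificity, and the area under the receiver operating characteristic curve (AUROC"), in the internal and external test sets. Accuracy, precision and F1 are secondary.
- Section 2.9 (Sample size) repeats that "binary predictions are warranted for each subgroup of BCL".
- Section 2.10 (Statistical analysis) says that "the ROC curve for binary classification will be plotted and AUROC will be calculated".

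Sections 2.2 and 2.3 enrol consecutive kyphoplasty patients, and no criterion removes those without a leak. The article does not say in words who forms class 0, or how a patient with more than one type of leak is coded.

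Two further analyses in section 2.10 bear on subtype: "The confusion matrix of DL model and readers in detecting Type I–IV of BCL will be used to evaluate the predicting performance", and a "Linearly weighted Cohen’s kappa coefficient between Reader 3, Reader 4, and the DL model with the reference standard". The layout of neither is stated. Each could be one multi-category table or a set of two-by-two tables.

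Subtyping is a headline aim. The Abstract and Introduction promise prediction of both occurrence and class of leak. The Discussion faults earlier models for "a lack of subtyping for BCL" and says that "our model not only predicts the occurrence of BCL during PKP, but also enables further subtypes of leakage".

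**The concern.** With one 0/1 output per subtype and all patients in the test set, the negatives for, say, Type IV are patients with no leak plus patients with Type I, II or III only. When leaks are uncommon, most negatives are leak-free. The AUROC for Type IV then mainly reflects how well the score separates leak from no leak, with little weight on separating Type IV from the other types.

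A model that recognises only a vertebra likely to leak could therefore report respectable figures for all four subtypes. A reader would take these as evidence of subtype prediction, the stated advance over earlier work, although the four outputs might carry the same information. Planning aimed at one leak type would then rest on a distinction that no primary result had isolated.

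**Working it through.** The plan gives no target AUROC, expected leak rate or subtype mix, so there is no figure of its own to reproduce on this point. The check asks what the primary measures would show for a score with no subtype information.

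**Inputs**
- Any-leak rate L: the Introduction reports "incidence rates ranging of 5–80" per cent from the literature. No rate is given for this cohort.
- Any-leak AUROC A: the Discussion cites 0.8819 for the best model in one earlier study and 0.633 to 0.898 across models in another. I use 0.8819 (about 0.88), with 0.633 as a low value and 1 as the limit.
- Share of patients with subtype k, p: not given. I assume four equally common, exclusive types, so p = L/4, and then vary this.

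**Formula.** A fraction (1−L)/(1−p) of the negatives is leak-free, and against them the score has AUROC A. The remaining (L−p)/(1−p) leaked with another type, and against them it has 0.5. Hence

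AUROC_k = [A(1−L) + 0.5(L−p)] / (1−p).

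At L = 0.30, p = 0.075, A = 0.8819: (0.8819×0.70 + 0.5×0.225)/0.925 = (0.6173 + 0.1125)/0.925 = 0.789.

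| Leak rate | A = 0.633 | A = 0.8819 | A = 1 |
|---|---|---|---|
| 5% | 0.628 | 0.867 | 0.981 |
| 20% | 0.612 | 0.822 | 0.921 |
| 30% | 0.601 | 0.789 | 0.878 |
| 50% | 0.576 | 0.718 | 0.786 |
| 80% | 0.533 | 0.595 | 0.625 |

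**Simulation check** (400,000 patients, A = 0.8819). At 30% leak the one-versus-rest AUROC is 0.789, and among leakers it is 0.501. At 80% the figures are 0.597 and 0.501. The leak-only contrast exposes the absence of subtype information at either leak rate.

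**Sensitivity to the subtype mix.** At 30% leak and A = 0.8819, a subtype making up 10% of leaks gives 0.776 and one making up 50% gives 0.815. If a quarter of leakers have a second type, spread evenly, p = 0.30×1.25/4 = 0.094 and the result is (0.6173 + 0.5×0.206)/0.906 = 0.795.

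**How far the effect reaches.** A subtype AUROC of at least 0.80 without subtype information needs a leak rate of about 27% or less at A = 0.8819, and about 47% or less even for a perfect any-leak score.

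**Sensitivity and specificity.** Take normal scores with A = 0.88 (separation 1.662 standard deviations) and a cut-off with 80% specificity in leak-free patients. Sensitivity is 0.794 for every subtype. At 30% leak, the leak-free share of negatives is 0.70/0.925 = 0.757, so subtype specificity is 0.757×0.80 + 0.243×0.206 = 0.656.

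**Precision.** In that example precision is 0.075×0.794/(0.075×0.794 + 0.925×0.344) = 0.16. Low precision is not diagnostic, however. A genuine subtype classifier with 80% sensitivity and 80% specificity has 0.060/(0.060 + 0.185) = 0.245 at the same prevalence, and a perfect any-leak rule has 0.25.

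**The case against.** The strongest reply is that one-versus-rest is the right primary question. Before surgery nobody knows who will leak. The Abstract and Discussion describe use of the model to flag patients likely to have a given type of leak, so its performance among all candidates is what matters. Restricting to leakers conditions on a later event. This stands, and the primary measures should stay.

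A reader might infer that subtyping is never tested. The documents do not support that. Other leak types are among the negatives, so cross-type errors lower both AUROC and specificity. A multi-category confusion matrix would show such errors directly. Linear weights change nothing in a two-category kappa, which hints that a multi-category table may be intended. With the layout unstated, this is ambiguity rather than absence. A multi-category kappa would still mix agreement on leak with agreement on type.

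A reader might also infer that any leak detector would look good on all four subtypes. It would not. At 80% leak even a perfect any-leak rule reaches an AUROC of 0.625 with specificity (1−0.80)/(1−0.20) = 0.25. With A = 0.633 the subtype figures never exceed 0.63. The Discussion stresses that leak rates can be high, and reports that the earlier deep learning model did worse than the best model, the source of the 0.8819.

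Nothing suggests that the four outputs will in fact collapse into one score. The calculation shows what the primary measures could not rule out.

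An extra secondary contrast could sit in an analysis plan that is not shown. The point is narrower: the article states both a primary outcome and a claim, and the first does not by itself carry the second.

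**Conclusion.** The concern holds in a limited form. Read naturally, the primary measures are one-versus-rest among all kyphoplasty patients. That reading is an inference, because class 0 is not defined. They answer who is at risk of a given subtype, but no stated primary measure separates subtype discrimination from any-leak detection.

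In size, a score with no subtype information and any-leak AUROC 0.88 would show 0.87 per subtype at 5% leak, 0.79 at 30% and 0.60 at 80%, against 0.50 among leakers. This rests on four equally common, exclusive types; unequal types move the 30% figure only between 0.78 and 0.82. The problem is material when leak rates are low to moderate and the any-leak model is strong, and it fades near 80%. It does not make the primary outcome wrong. It limits what may be concluded about subtyping, and a cheap addition removes the limit.

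**What to change.** Keep the one-versus-rest measures as primary. In sections 2.8 and 2.10:

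1. State that class 0 for a subtype is every patient without that subtype. Code each subtype as present or absent, so that a patient with several types counts as positive for each.
2. As secondary analyses in both test sets, report for each subtype, with 95% bootstrap intervals: (a) the AUROC among patients with a reference-standard leak, subtype present versus absent; (b) the paired difference in one-versus-rest AUROC between the subtype output and an any-leak score, such as the maximum of the four outputs.
3. Claim subtype discrimination beyond leak detection only where the lower limit of (a) exceeds 0.5 and that of (b) exceeds zero. Otherwise report risk prediction for that subtype without that claim.

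The cost is a few sentences and a little code on outputs already produced, with no new patients or readings. The downside is precision. Test-set sizes are not stated, but with an assumed 50 patients, 30% leaking and four equal types, (a) would compare about 4 patients with 11. Intervals will be wide, and the subtype result may look less favourable. The AUROC in (a) also depends on the mix of the other leak types, so that mix should be reported for each test set.
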